#### Secondary study parameter(s)

Time-to-diagnosisTime-to-diagnosis will be defined as the period from the date of the index MRI result to the date of the start of the final treatment. A Kaplan–Meier analysis will be performed. Groups will be compared with use of the log-rank test.Overall survivalOverall survival will be defined as the period from the date of the index MRI result to the date of death. A Kaplan–Meier analysis will be performed. Groups will be compared with use of the log-rank test.Number of unnecessary treatment cyclesThe number of unnecessary treatment cycles of chemotherapy and bevacizumab will be calculated for both groups. The scores of both groups will be compared by means of the Mann–Whitney *U* test. Cost-effectivenessCost-effectiveness of the study arms will be determined from a societal perspective. Life years, QALYs, and costs will be assessed (See “Plans for assessment and collection of outcomes”). Direct and indirect costs will be included in the analysis. If benefits and costs are expected to persist beyond trial time horizon, a decision analytic model will be built. If not, a trial-based economic evaluation will be conducted.The cost-effectiveness analysis will be conducted in adherence to the 2024 version of the Dutch guidelines for economic evaluations [25].Outcome of the cost-effectiveness analysis will be expressed as incremental Costs, incremental Quality-Adjusted Life Years (QALY), and Incremental Cost-Effectiveness Ratio (ICER). The results of the cost-effectiveness analysis will be combined with observed and extrapolated uptake to estimate the budget impact over time. The budget impact analysis (BIA) will be performed according to the Dutch guidelines and the BIA guideline (“BIA leidraad”) and BIA calculation tool will be utilized [29].Health-related quality of lifeThe secondary outcome HRQOL will be captured and assessed as a continuous measure by EORTC QLQ-C30 and BN20 questionnaires through timepoint analyses at *t* = 6 weeks and *t* = 6 months. Compound scores will be calculated for each patient according to the standard scoring algorithms for these questionnaires [21, 23]. Group comparisons at these timepoints will be conducted using Student’s *t* tests. Results will be interpreted in terms of statistically significant difference and clinical relevance between study arms. Statistical difference will be assessed via a two-sided *p*-value ≤ 0.05. Additionally, secondary HRQOL will be evaluated longitudinally as a continuous measure using a mixed model for repeated-measures analysis, examining changes in individual patients’ raw scores over time. Previous literature indicates HRQOL analyses become unreliable when the response rate falls below 60% of all participants [30]. Should this occur, data analysis will be limited to the timepoints that meet the 60% response criterion.PET characteristics to predict clinical outcomeIn the intervention arm, we will perform exploratory analyses of the PET characteristics, both from static and (if available) dynamic PET images, such as SUV values and SUV ratio’s, as predictors of overall survival and progression-free survival, by cox analyses.Other study parametersLastly, determinants of unnecessary interventions will be investigated, including effect modifiers of the effect of [^18^F]FET PET on outcome. In order to answer this research question, a multivariable logistic regression analysis will be performed.

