## Introduction

### Background and rationale {6a}

Glioblastomas are incurable progressive brain tumors with a variable, but poor prognosis. After surgery, chemoradiation with concomitant and adjuvant temozolomide chemotherapy offers effective, albeit temporary, palliation for many patients, with median overall survival of 14–16 months [1, 2]. In the months following radiotherapy, ~ 50% of patients will develop changes on MRI, suggestive of recurrence. In a majority of these patients, these MRI changes are classified as pseudoprogression [3]. Pseudoprogression is defined as treatment-induced increasing, or new, contrast enhancement which is mostly self-limiting and requires a different management strategy than tumor recurrence. Pseudoprogression will be used in this paper as an encompassing term that includes radionecrosis and other treatment-related effects after (chemo-)radiotherapy. Discrimination between pseudoprogression and tumor progression on MRI can be notoriously challenging [4]. In the patients that are eventually diagnosed with pseudoprogression, initial diagnostic uncertainty is common, which may lead to an increased risk of misdiagnoses and unnecessary interventions [5, 6].

Currently, in the Netherlands, in these patients with diagnostic uncertainty on MRI, the multidisciplinary team prefers to wait for a next scan in 6–12 weeks’ time for definitive diagnosis, leading to potential delay of diagnosis and adequate management and causing psychological burden for patients and their relatives with impact on quality of life [7].

The use of positron emission tomography (PET) with the radioligand [^18^F]Fluoro-ethyl-tyrosine, or [^18^F]FET PET in short, has the potential to differentiate treatment-related changes from tumor recurrence with higher accuracy compared to current clinical standard MRI including perfusion-weighted MRI [8–10]. Meta-analyses of literature confirm that addition of [^18^F]FET PET to MRI has higher diagnostic accuracy for differentiation of pseudoprogression from tumor recurrence compared with MRI alone [11, 12]. Recent literature has led to evidence-based recommendations by the Response Assessment in Neuro-Oncology (RANO) working group to add [^18^F]FET PET imaging to MRI in cases with diagnostic uncertainty [13].

However, this advice is not based on prospective randomized patient benefit- or cost-effectiveness studies, as neither have been performed.

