### Intervention description {11a}

Patients in the investigational arm will undergo the extra [^18^F]FET PET scan, with use of the O-(2-^18^F-fluoroethyl)-L-tyrosine ([^18^F] FET) tracer. The tracer will be provided free of charge by Curium™ for a subset of the patients (based on logistical availability and scheduling per patient). For this study, Curium™ does not have a role in the design, execution, analysis, interpretation, manuscript writing and/or decision to publish.

[^18^F]FET PET scanning will be performed according to the joint European Association of Nuclear Medicine (EANM)/European Association of Neurooncology (EANO)/Response Assessment in Neurooncology (RANO) guideline [20]. In most patients, a static scan (20–40 min post-injection) will be performed. Patients will be asked for additional (opt-in) consent to undergo a dynamic [^18^F]FET PET scan. If the logistics of the research site allow for this scan, these patients will undergo dynamic scanning (continuous scanning 0–40 min post-injection). Interpretation will be done by a nuclear medicine physician from the local center according to current European guidelines [20]. Central review will be performed by a panel of nuclear medicine physicians from the study team, specialized in [^18^F] FET PET scans.

Patients are treated according to current standard-of-care that is determined by the treating physician/multidisciplinary team, but will be based on the diagnosis from the static [^18^F]FET PET findings:In case of [^18^F]FET PET-diagnosis of tumor recurrence: a change in treatment regime will be made. Redo-debulking will be done only for clinical indications, including mass reduction or cytoreduction.In case of [^18^F]FET PET-diagnosis of pseudoprogression, or equivocal results: the ongoing treatment or observation will be continued, with addition of steroids and/or bevacizumab if needed for symptom relief. Redo-debulking will only be done for the rare indication of refractory symptoms of mass effect due to pseudoprogression.

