#### Secondary outcomes

Time-to-diagnosis (defined from the date of the index MRI result to the date of eventual management, including watchful waiting).Overall survival (defined from the date of the index MRI result to the date of death).Number of unnecessary treatment cycles during 6 months follow-up period (chemotherapy, bevacizumab).Cost-effectiveness, expressed in terms of incremental costs, incremental Quality-Adjusted Life Years (QALY), and Incremental Cost-Effectiveness Ratio (ICER). This is measured from a healthcare and societal perspective with use of three questionnaires: the iMTA Medical Consumption Questionnaire (iMCQ), the iMTA Productivity Cost Questionnaire (iPCQ), and EuroQol 5D-5L (EQ-5D) at *t* = 6 weeks, *t* = 12 weeks, and *t* = 6 months.HRQOL (continuous measure): EORTC-QLQ-C30 + BN20 at *t* = 6 weeks and *t* = 6 months (preferably before follow-up imaging is performed).PET characteristics as predictors of overall survival and progression-free survival outcomes.Determinants of unnecessary interventions.

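### Time-to-diagnosis has two incompatible end dates, and neither is the date on which the diagnosis is made

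*Protocol article*

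**What the plan says.** The secondary objectives {7} ask whether adding FET PET shortens time-to-diagnosis, and the Discussion hypothesises a faster accurate diagnosis. The endpoint is then defined twice.

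- Outcomes {12}, Secondary outcomes: "Time-to-diagnosis (defined from the date of the index MRI result to the date of eventual management, including watchful waiting".
- Statistical methods {20a}, Secondary study parameter(s): the clock again starts at the index MRI result but runs "to the date of the start of the final treatment". The analysis follows directly: "A Kaplan–Meier analysis will be performed. Groups will be compared with use of the log-rank test".

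Three other places bear on how these definitions work in practice.

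- Background and rationale {6a}, on current Dutch practice under diagnostic uncertainty: "the multidisciplinary team prefers to wait for a next scan in 6–12 weeks’ time for definitive diagnosis".
- Intervention description {11a}, on what follows a PET diagnosis of pseudoprogression or an equivocal PET: "the ongoing treatment or observation will be continued, with addition of steroids and/or bevacizumab if needed for symptom relief".
- Table 1 puts randomization at about days 5–16 and the PET result at about days 10–33, counting the index MRI result as day 1. Final diagnosis is recorded at month 6.

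**The concern.** Both definitions start at the index MRI result, so they differ only in the end date. One admits watchful waiting as an end point; the other requires a treatment to start. A patient who is observed and never treated has an event under the first and none under the second.

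Both also date management, while the objective is about diagnosis. In this population the two come apart. Waiting is often chosen because the diagnosis is not yet known, and a diagnosis of pseudoprogression often leads to no new treatment.

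What is at stake is the answer to a stated secondary objective. The same patients could show a clear gain, a weak one or, under one reading, a loss, depending on which sentence is followed. The trial is open-label, so an end date still unsettled at analysis could be chosen with the results in view.

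**Working it through.** The article gives no figure for time-to-diagnosis, so there is none to reproduce.

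**Step 1. The two rules applied to typical patients**

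| Patient | Outcomes wording | Statistical methods wording | Diagnosis made |
|---|---|---|---|
| PET arm, recurrence, treatment changed | Date of new management | Start of new treatment | About days 10–33 |
| PET arm, pseudoprogression, observation continues | Date observation is settled on | No event | About days 10–33 |
| Control, board waits, later scan shows progression | Date of the wait decision, or date after the scan | Start of new treatment | About days 42–84 |
| Control, board waits, later scan shows pseudoprogression, observation continues | Date of the wait decision, or date after the scan | No event | About days 42–84 |

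The control dates use the 6–12 weeks in the Background: 6 × 7 = 42 and 12 × 7 = 84 days. Patients who simply continue ongoing chemotherapy fall in the same position as those who are observed.

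**Step 2. The contrast that the objective has in mind**

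The midpoint of days 10–33 is (10 + 33)/2 = 21.5. The midpoint of days 42–84 is (42 + 84)/2 = 63. A diagnosis-based endpoint would therefore separate the arms by about 63 − 21.5 = 41.5 days.

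**Step 3. Illustrative simulation**

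This uses 72 patients per arm, 150 runs per scenario and a log-rank Z in which positive values mean PET is faster.

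- From the article: PET-arm date uniform on days 10–33; control diagnosis uniform on days 42–84.
- Assumed: interim control wait decision uniform on days 1–16; censoring at day 183; observed pseudoprogression in 30% or 60% of patients; treatment for progression starts on the day of diagnosis; no deaths.
- Also assumed: a varying share of controls is dated at the wait decision and the rest at the next scan, while no interim wait decision counts in the PET arm.

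*End date = diagnosis.* Medians are about 22 days (PET) and 62 days (control), with mean Z about +13.

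*End date = start of final treatment.* Expected events are 144 × (1 − p), where p is the share observed for pseudoprogression:

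- p = 0.30: 144 × 0.70 = 100.8 events, mean Z about +3.
- p = 0.60: 144 × 0.40 = 57.6 events, mean Z about +1, median not reached in either arm.

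*End date = eventual management, with an interim wait decision counted as the event:*

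| Share of controls dated at the wait decision | Mean Z | Median days, PET vs control |
|---|---|---|
| 30% | about +7 | 22 vs 53 |
| 50% | about +4 | 21 vs 16 |
| 70% | about 0 | 21 vs 12 |
| 90% | −4.6 | 21 vs 9 |
| 100% | −10.6 | 21 vs 8 |

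*End date = eventual management, read as settled management after the scan, with observation admitted.* Event dates then fall at or near the diagnosis, so the reversal does not arise.

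**The case against.** The best defence is that the two wordings were meant to agree. *Eventual* in one place and *final* in the other both point to settled management, and Other study parameters separately mentions initial management after imaging. On that reading, naming watchful waiting only makes clear that observation can be the settled choice. Observed patients then have an event and interim waiting is not one. This is a reasonable guess at the intention, and it removes the reversal. However, the statistical section still asks for the start of a treatment, and nothing in the text tells the person extracting dates which reading applies.

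Four stronger inferences are tempting, and the article does not support them.

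- *The endpoint will make PET look slower.* That requires ignoring *eventual* and, under the assumptions above, dating more than about 70% of controls at an interim wait decision. The article says that teams prefer to wait but gives no percentage.
- *Control wait decisions made before randomization create the bias.* Before allocation there are no arms, so such decisions would occur equally in patients later assigned to PET. The asymmetry needs decisions dated after allocation, or a rule that ignores them in the PET arm only. The simulation assumes such a rule, so its negative values mark the unfavourable extreme.
- *A majority of patients would have no event.* The majority in the Background describes MRI changes in the months after radiotherapy. The trial enrols at 3 months or later, at first uncertainty, with lesions of at least 1 cm. In addition, steroids or bevacizumab may be added in pseudoprogression, so some of these patients might be counted as starting a treatment.
- *The Kaplan–Meier analysis would be uninterpretable.* Patients who never start treatment and are followed to the end produce a plateau. The curve can be read as time to treatment, but it is not the endpoint named.

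It is also fair to say that censoring rules and the handling of death are commonly left to a statistical analysis plan; no finding is made on those.

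**Conclusion.** The point holds as a contradiction within the article. One secondary endpoint has two incompatible end dates, and neither is the date of diagnosis.

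Under the statistical methods wording, followed literally, whether a patient can have an event depends on the diagnosis itself. The proportion without an event is unknown, because no pseudoprogression share is given for the trial population. For the assumed range of 30% to 60%, it is 30% to 60% of patients, and the apparent PET advantage weakens without reversing.

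Under the outcomes wording, the effect ranges from none (settled management) to a reduced and possibly reversed advantage (interim waiting counted for most controls). These sizes rest on the assumptions in the working and are illustrations, not predictions.

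The endpoint is secondary and lies outside the hierarchical test of the two primary endpoints. The primary endpoints and the sample size are unaffected.

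**What to change.** Put one end date in both Secondary outcomes and Secondary study parameter(s): the date on which the multidisciplinary board first records a definite diagnosis, either tumor progression or pseudoprogression, whether or not treatment changes. Add two clarifications.

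1. Watchful waiting while the diagnosis is still uncertain is not an event.
2. Observation chosen after a diagnosis of pseudoprogression is dated at that diagnosis.

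Report agreement between this first recorded diagnosis and the 6-month final diagnosis separately, or as a sensitivity analysis. Making later confirmation a condition of the event would mix accuracy with timing and leave the date undefined for patients without a 6-month final diagnosis.

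The cost is a wording change in two sections and one extra date field. That date is not clearly collected now: the listed board notes cover uncertainty and initial management, and Table 1 records the final diagnosis at month 6. It would have to be extracted from the board notes. Recruitment is expected to run until December 2027, so the field can be added now and completed from existing notes for patients already enrolled.

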#### Secondary objectives

To determine, in glioblastoma patients with diagnostic uncertainty between pseudoprogression and tumor progression on a follow-up MRI after concomitant chemoradiation (“index MRI”), whether clinical management guided by an additional [^18^F]FET PET scan, when compared to management based on MRI only, leads to:Cost-effective interventionShorter time-to-diagnosis Changes in overall survival Lower number of unnecessary treatment cyclesImproved HRQOL over time (continuous measure), measured at t=6 weeks and t=6 months.

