#### Other study parameters

Patient characteristics: sex, age.Oncological characteristics: date of diagnosis of initial tumor, O^6^-methylguanine DNA methyltransferase (MGMT) promotor methylation status, CDKN2A/B-status, Karnofsky performance score at baseline and during clinical examination moments.Questionnaires EORTC-QLQ-C30 + BN20, EQ-5D, iPCQ and iMCQ at baseline, measured between informed consent and randomization.Diagnostic- and treatment characteristics: surgical- and concomitant chemoradiation characteristics, usage of bevacizumab, dosage of dexamethasone, follow-up scans, blood tests.Final diagnosis during follow-up after study intervention: tumor recurrence or pseudoprogression.Notes from multidisciplinary meetings, describing diagnostic uncertainty and initial management after diagnostic imaging.

The schedule of assessments is illustrated in Table 1.

**Table 1 Tab1:** Schedule of assessments

Visit	Index MRI result	Informed consent	Randomization	FET PET^a^	FET PET result^a^				
Study time	Day 1	± Days 3–14	±Days 5–16	± Days 7–30	± Days 10–33	Week 6	Week 12	Month 6	End of trial
Unnecessary interventions								X	
EORTC-QLQ-C30 + BN20/EQ-5D/iPCQ/iMCQ		X				X	X	X	
Karnofsky performance score	X				X^a^				
Final diagnosis								X	
Survival status								X	X^b^
Healthcare consumption								X	
Adverse events^c^				X	X				

^a^The intervention group only

^b^A survival sweep will be performed at the end of the trial

^c^All possibly/probably related adverse events will be reported for 30 days in both groups. All serious adverse events will be reported for 7 days in both groups

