### Sample size {14}

From current practice (survey among the participating centers), we estimate that 37% of the glioblastoma patients that meet our inclusion criteria, eventually undergo unnecessary interventions (control arm). In the intervention arm, we expect this proportion to be much lower (~ 12% from clinical scenarios), due to the high accuracy of [^18^F]FET PET. Using a two-sided *Z* test with pooled variance with an alpha of 0.05, based on a power of 90%, we need 61 patients in each arm, so 122 in total. Due to the intention-to-treat set-up and unnecessary treatment as outcome measure, we expect that virtually all patients can be included in final analysis, with minimal drop-out. For the co-primary endpoint of HRQOL (EORTC-QLQ-C30 + BN20) at *t* = 12 weeks, drop-out due to missing questionnaire data is estimated at 10%. With addition of this drop-out rate, we will randomize 144 patients, 72 patients per study arm.

Methodologically, the two primary endpoints are hierarchical: the first (unnecessary interventions) must be met before the second (HRQOL) is formally tested. Since HRQOL may be influenced by earlier diagnosis from FET PET, the primary endpoint of unnecessary interventions should be met first to obtain a HRQOL result which is not caused solely by such a timing effect. This justifies a fixed-sequence testing approach—each tested at *p* = 0.05. If the first test is not significant, HRQOL results will be considered exploratory. The sample size was powered for the first endpoint, with a 10% increase to account for potential missing HRQOL data; a formal power calculation for HRQOL was not feasible due to limited prior data.

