### Methods for additional analyses (e.g., subgroup analyses) {20b}

As treatment center will be used for stratification and it is expected that some of the centers will recruit small numbers of patients, no adjusting for this stratification factor will be performed in the primary analysis. However, a correction analysis for treatment center will be performed as sensitivity analysis. In addition, correction analyses for MGMT promoter methylation status (methylated versus unmethylated versus unknown), Karnofsky performance score (< 70 vs ≥ 70), and prior surgical procedure (biopsy versus resection) will be performed as sensitivity analyses [31].

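### The main overall survival comparison is an unadjusted log-rank test; a pre-specified covariate-adjusted hazard ratio with its interval would use baseline data already collected and report more

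*Protocol article*

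**What the plan says.** Overall survival is a secondary outcome, counted from the index MRI result to death. The objective is stated without direction: "Changes in overall survival" (Objectives {7}). Under Secondary study parameter(s), the analysis is Kaplan–Meier, and then "Groups will be compared with use of the log-rank test". No stratum, covariate, hazard ratio or confidence interval is named for this comparison. The same section does plan Cox analyses of survival, but only for PET characteristics within the intervention arm.

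Sequence generation {16a} stratifies the block randomisation by treatment centre and by nothing else. Other study parameters lists "Patient characteristics: sex, age" along with MGMT status, Karnofsky score at baseline, and surgical characteristics.

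Methods for additional analyses {20b} first explains that centre will not be adjusted for in the primary analysis, because some centres will be small, but will be corrected for as a sensitivity analysis. It then adds corrections for MGMT status (methylated, unmethylated, unknown) and for "Karnofsky performance score (< 70 vs ≥ 70), and prior surgical procedure (biopsy versus resection) will be performed as sensitivity analyses". It does not name the outcomes to which these corrections apply, and age is not among them.

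On size, Sample size {14} says "The sample size was powered for the first endpoint", meaning unnecessary interventions. No death count, hazard ratio or power is given for survival.

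**The concern.** With 72 patients per arm and stratification by centre only, the four patient-level factors are balanced by chance alone. The plan itself treats three of them as worth correcting for. Its reason for not adjusting, small centres, applies only to centre. It gives no reason for keeping patient-level factors out of the main survival analysis.

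If these factors predict survival, leaving them out costs some power, and the unadjusted hazard ratio lies nearer to 1 than the hazard ratio among patients with the same baseline values. A non-directional objective also calls for an estimate with an interval, and a log-rank p-value does not show how much benefit or harm the data exclude.

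This matters because PET findings direct treatment in the intervention arm. Serious adverse events are collected for 7 days and related adverse events for 30 days, and there is neither an interim analysis nor a data monitoring committee. Among the planned outcomes, survival is the most direct check on later harm from PET-guided management.

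**Working it through.** **1. The plan's own figure.** The only sample size calculation is for unnecessary interventions. The control-arm input reads "we estimate that 37% of the glioblastoma patients that meet our inclusion criteria"; the intervention-arm input is "12% from clinical scenarios". The method is a two-sided Z "test with pooled variance with an alpha of 0.05, based on a power of 90" per cent. With p1 = 0.37, p2 = 0.12 and mean 0.245:

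n = [1.96·√(2·0.245·0.755) + 1.2816·√(0.37·0.63 + 0.12·0.88)]² / 0.25² = (1.192 + 0.746)² / 0.0625 ≈ 60.1, so 61 per arm.

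This reproduces the stated 61 per arm (122 in total). It carries no information about survival.

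**2. Survival power from trial size alone.** Schoenfeld's formula with 1:1 allocation gives power = Φ(√d/2·|ln HR| − 1.96), where d is the number of deaths. The document gives no d, so 100 is an assumption and 144 is the ceiling.

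| Deaths | HR 0.6 | HR 0.7 | HR 0.8 |
|---|---|---|---|
| 100 | 72% | 43% | 20% |
| 144 | 87% | 57% | 27% |

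For example, with d = 100 and HR 0.7: 5 × 0.357 − 1.96 = −0.18, and Φ = 0.43.

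**3. What adjustment adds.** This was simulated with 144 patients, 1:1 allocation and 3,000 runs per setting. All of the following are assumptions that are not in the document:
- exponential survival, with a control median of 10 months at reference covariates;
- censoring uniform over 6 to 42 months, giving about 93 to 108 deaths;
- 40% MGMT methylated, 20% with low Karnofsky score, 25% biopsy only, and age standardised.

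Covariate hazard ratios, in the order MGMT methylated, low Karnofsky score, biopsy, age per SD:
- weak: 0.8, 1.2, 1.1, 1.1;
- moderate: 0.6, 1.6, 1.4, 1.25;
- strong: 0.45, 2.0, 1.6, 1.4.

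Power of the log-rank test against the Cox model adjusted for all four factors:

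| Conditional HR | Weak | Moderate | Strong |
|---|---|---|---|
| 0.8 | 21.5% vs 22.1% | 17.7% vs 20.7% | 14.7% vs 18.5% |
| 0.7 | 40.7% vs 41.5% | 37.3% vs 43.5% | 30.8% vs 40.5% |
| 0.6 | 67.6% vs 68.0% | 63.8% vs 69.0% | 55.8% vs 68.1% |

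The differences are 0.4 to 0.8 points (weak), 3.0 to 6.2 (moderate) and 3.8 to 12.3 (strong). With a true hazard ratio of 1, the rejection rate was 4.8 to 5.5% for the log-rank test and 5.5 to 6.1% for the adjusted model. With strong covariates and a conditional hazard ratio of 0.70, the unadjusted estimate averaged about 0.74.

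**4. What an interval would show.** For an estimate of exactly 1, the approximate 95% limits are exp(±1.96·2/√d). With d = 100 this is exp(±0.392), or 0.68 to 1.48. With d = 130 it is exp(±0.344), or 0.71 to 1.41. A non-significant log-rank result would therefore leave a wide range of benefit and harm open, and the p-value alone does not show that range.

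**The case against.** The strongest reply is that nothing stated is wrong. Under randomisation the unadjusted log-rank test is valid, survival is an unpowered secondary outcome, and the choice matches the trial's general pattern of simple main tests with adjusted sensitivity analyses. This stands, and it limits the point to an improvement.

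A reader might infer that survival will never be adjusted. The document does not support that. The correction analyses sit under a general heading and are not restricted to one outcome. The phrase about the primary analysis occurs in the sentence on centre and may simply contrast with a sensitivity analysis. The scope is ambiguous, and three of the four factors are already planned. On either reading, though, adjustment is not the main survival analysis, and age is absent.

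A reader might also take a substantial loss of power as established. It is not, because every survival and covariate input is assumed. Part of the simulated gain may reflect the adjusted test's slightly higher rejection rate under the null, which is worth about 1 to 2 points. Power is limited mainly by trial size: in these runs adjustment brings it to no more than 44% at a hazard ratio of 0.7 and 22% at 0.8.

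The pull of the unadjusted hazard ratio toward 1 is a difference in estimand, not bias, since hazard ratios are non-collapsible. Nor is there evidence that cutting Karnofsky score at 70 costs anything here: the simulation used a two-level score and cannot show it.

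Finally, an article may leave the reporting of a hazard ratio and its interval to a fuller document. That is fair, and the absence of a hazard ratio is not counted here as an omission. The point rests on the main comparison that the article does fix.

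**Conclusion.** The point holds as a recommendation on efficiency and reporting. The article fixes an unadjusted log-rank test as the main survival comparison. Four recorded baseline factors are not stratified for, and the planned corrections are secondary, unclear in scope and without age.

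Under the stated assumptions the gain in power is about zero if the factors are weakly prognostic, 3 to 6 points if moderate and roughly 4 to 12 points if strong. The documents do not say which case applies. The reporting gain, a hazard ratio with its interval, does not depend on covariate strength.

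The documents do not support calling the log-rank test invalid or biased, or saying that the survival conclusions would change. The primary endpoint and its sample size are unaffected.

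**What to change.** State in the protocol or analysis plan that the main overall survival estimate comes from a Cox model with arm, MGMT status (methylated, unmethylated, unknown), baseline Karnofsky score, prior surgery (biopsy, resection) and age, reported as a hazard ratio with a 95% confidence interval. Keep the Kaplan–Meier curves and the log-rank test as the supportive marginal comparison. Say which outcomes the correction analyses in {20b} cover.

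The Karnofsky covariate should be the value recorded at the index MRI: Table 1 schedules a further score at the PET result in the intervention arm only, and that one falls after randomisation. Using the score ungrouped is optional, since no gain from it has been shown.

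The cost is a few sentences and one model, with no new patients or data items. The downsides are that the hazard ratio becomes conditional on the covariates, that the model adds assumptions, and that the covariates must be fixed in advance. The last is best done soon: recruitment is expected to run to December 2027 and the trial is unblinded, so covariates chosen later could be seen as selected.
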